## **9.6 Bowel Function and Quality of life Assessment**

Function and QoL will be assessed at registration, at re-staging after TNT, and at the following long term follow-up time points: 3-6, 9-12, 21-24 and 36 months +/-30 days Patients will receive one survey packet, including 32-45 items depending on patient gender and the presence of a stoma. We will use the 19-item Bowel Function Index (BFI) (available at <http://www.ncbi.nlm.nih.gov/pubmed/15868235>) to assess bowel function.[44] The psychometric properties of the instrument have been previously published [44] and all subscales and total score show good internal consistency (Cronbach's alpha: Frequency 0.75, Dietary 0.75, Soilage 0.78) and test-retest reliability (TOTAL 0.84 , Frequency 0.74, Dietary 0.62, and Urgency/Soilage 0.87).

All patients without a stoma will also complete 5 additional questions from the Low Anterior Resection Scale. The Low Anterior Resection Score (LARS) is a newly developed and validated 5 question index that was specifically developed to categorize bowel dysfunction after low anterior resection in Europe. Most recent use of the LARS data shows a good correlation and a high sensitivity (72.5%) and specificity (82.5%) for major LARS (poor function). Discriminant validity showed significant differences between groups expected groups. [97, 98] The use of LARS will allows us to compare our results to European groups. In the LARS Score patients are asked to describe symptoms which best describe daily life. There is no specific time period, but at most the averages are over the past week. The LARS score has a range of 0-42 with 0-20 being No LARS, 21-29 being Minor LARS, and 30-42 being Major LARS.

APR patients will complete 10 items from the BFI which is currently being used by others (2R01CA106912-04) and appears to have good psychometric properties. We will also use the 21-item Stoma QoL for patients undergoing an APR for descriptive purposes.[90] To assess sexual function, we will use gender-specific questionnaires: 5-item International Index of Erectile Function (IIEF-5), and 6-item Female Sexual Functioning Index. [91-93] Bladder function will be assessed using two items from validated questionnaires (the Prostate Health Related QOL questionnaire and the International Prostate Symptom Score (IPSS)).

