In addition, we will calculate therapy compliance using the following measures: the number of days RT was held, the number of RT delays of  $\geq 1$  week, the number of dose delays and the number of dose reductions in INCT and CNCT. We will also calculate the rate of select hematologic events (as outlined in 17.2), select non-hematologic events (as outlined in 16.0), and unexpected Grade 3 or higher non-hematologic adverse events and surgical complications in each treatment arm. Comparisons will be done using the Wilcoxon Rank Sum test or the Fisher’s Exact test.

**14.3 Secondary objective 2.:** *To measure patient-reported functional outcomes and QoL in patients with LARC treated with NCT, CRT and NOM, and compare these to patients treated with TME.*

The primary analyses for this aim will use data combined across both treatment arms; however, differences according to treatment will also be investigated. The primary endpoint will be QoL as measured one year from the end of TNT. Secondary endpoints will be bowel, sexual, and bladder function. While the subscales will be reported, the primary secondary endpoints will be the total scores on the BFI, FSFI and IIEF. With a total of 325 patients accrued, we expect that 129 patients will obtain complete clinical response and 196 will undergo TME. Approximately 15 to 30 patients initially treated with NOM are expected to cross over to TME at some point during follow-up. For the primary analyses, the NOM group will include these cross-overs on an intent-to-treat analysis. In secondary analysis, patients who eventually crossed over to receive surgery will be included in the TME group. We define this analysis as a comparison between TME vs. durable NOM. Durable NOM is defined as 3-year disease-free survival. We expect that 70% of patients will complete the QoL assessment at 1 year. This response rate takes into account refusals to complete the QoL

questionnaires, and the approximately 20% of patients who will develop distant disease or die before the 1-year time point. Thus, at 1 year we expect to have information on 94 TME patients and 62 NOM patients.

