The primary endpoint of QoL will be assessed using the EQ-5D index, an overall measure of QoL and health ranging from 0 (worst health) to 1 (best health). Comparison will be done using the two-sample t-test. The minimally important difference (MID) for 534 cancer patients in the United States has been estimated to be in the range of .05 to .09 when using ECOG performance status as an anchor (Pickard, Neary, Cella 2007). The standard deviation of the EQ-index was .15 in this patient population. With our sample size of 156, we will be able to detect a difference of .07 with 80% power and type I error of 5%, assuming a standard deviation of .15.

In secondary analyses we will use a t-test to compare the EQ-5D index, measured at 1 year, in patients with durable NOM vs. TME. The differences in EQ-5D index from 1 year to 3 years will also be compared in patients with durable NOM vs TME, using an ANCOVA model that adjusts for variables found to be significantly different by NOM vs TME. Trends in the EQ-5D from baseline, 12, 24, and 36 months will be graphed, and evaluated descriptively.

Similar analyses will be done to study all other patient-reported functional and QoL endpoint.

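### The primary quality-of-life comparison of NOM with TME is an unadjusted t-test between groups formed by tumour response, so it is open to confounding and less precise than the collected EQ-5D data allow

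*Protocol*

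**What the plan says.** Section 14.3 (secondary objective 2) pools the two randomised arms and compares NOM with TME. On timing it says: "The primary endpoint will be QoL as measured one year from the end of TNT". The measure is the EQ-5D index, and the analysis is fixed in one sentence: "Comparison will be done using the two-sample t-test". No covariate is named. Patients who later cross over to surgery stay in the NOM group for this analysis.

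The secondary 1-year comparison, durable NOM against TME, is again a t-test. Only the difference from 1 to 3 years is adjusted, "using an ANCOVA model that adjusts for variables found to be significantly different by NOM vs TME". EQ-5D from baseline onward is otherwise graphed and described. The other functional and QoL endpoints are to be analysed in a similar way.

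Section 9.3.2 sends patients with a complete or near complete clinical response to NOM and the rest to TME. Section 15.2 randomises only the treatment sequence. Section 9.6 states: "Function and QoL will be assessed at registration, at re-staging after TNT", and EQ-5D-5L is part of that assessment.

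**The concern.** The two groups are responders and non-responders, so randomisation gives no assurance that they were alike beforehand. Section 3.3.2 itself lists earlier tumour stage among the factors on which the pathologic complete response rate depends, so some difference in baseline tumour extent is plausible. If that difference, or anything else linked to response, also affects EQ-5D, the t-test mixes it with the effect of having or avoiding surgery. Section 3.4 intends these data to inform patients choosing between the two options, a use that a raw contrast of means supports poorly.

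Selecting covariates by significance does not cure this. Whether a variable differs significantly between groups depends on sample size as well as on the imbalance, and says nothing about how strongly the variable predicts the outcome. A real confounder can be dropped, and the model is not known until the data are seen. The rule also leaves the primary comparison untouched.

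Precision is the lesser matter: a pre-treatment measurement of the same index is available and the test does not use it.

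**Working it through.** **Inputs from section 14.3.** SD: "The standard deviation of the EQ-index was .15 in this patient population". Group sizes: "at 1 year we expect to have information on 94 TME patients and 62 NOM patients", 156 in total. Claim: "we will be able to detect a difference of .07 with 80% power" and a 5% type I error, taken here as two-sided because the sentence does not say.

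**1. The stated power reproduces.** Detectable difference at 80% power = (1.960 + 0.842) × SD × √(1/n₁ + 1/n₂).
- 94/62: 2.802 × .15 × √(1/94 + 1/62) = 2.802 × .15 × .1636 = .069, which rounds to .07.
- Power for .07 is 81.4% (normal) or 80.9% (noncentral t), against 80% stated.

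**2. Group sizes at 325 patients.** The same section expects 196 TME and 129 NOM patients among 325, with 70% completing the 1-year form: .70 × 196 = 137 and .70 × 129 = 90. The stated 94 and 62 correspond to the earlier total (.70 × 222 = 155). With 137/90 the unadjusted detectable difference is 2.802 × .15 × √(1/137 + 1/90) = 2.802 × .15 × .1357 = .057. Both sets are carried forward.

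**3. Precision after adjusting for registration EQ-5D.** Residual SD = .15 × √(1 − r²), where r is the correlation between registration and 1-year scores. The protocol gives no r; .4 to .6 is an assumption.

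| r | Residual SD | Detectable, 137/90 | Detectable, 94/62 | Equivalent sample, 1/(1 − r²) |
|---|---|---|---|---|
| 0 (t-test) | .150 | .057 | .069 | 1.00 |
| .4 | .137 | .052 | .063 | 1.19 |
| .5 | .130 | .049 | .060 | 1.33 |
| .6 | .120 | .046 | .055 | 1.56 |

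A group difference in the registration score takes back a little of this. The variance is multiplied by 1 + p(1 − p)d², with d the gap in SD units. For a gap of .05, d = .05/.15 = .33 and p = 62/156, which gives 1 + .2395 × .111 = 1.027, or about 1.3% on the detectable difference.

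**4. Bias of the t-test for an assumed gap.** If registration means differ by g and the 1-year score has slope b on the registration score, the unadjusted difference is shifted by b × g.
- b = .5, g = .03: .015.
- b = .5, g = .05: .025, half the lower end of the quoted minimally important range (.05 to .09).

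Both b and g are assumptions.

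**5. Effect on the error rate if NOM and TME do not truly differ.** The standard error is .15 × .1636 = .0245 at 94/62 and .15 × .1357 = .0204 at 137/90. A shift of .015 to .025 raises the nominal 5% to about 9-17% at 94/62 and about 11-23% at 137/90. A larger sample shrinks the standard error but not the shift.

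**The case against.** A reader might infer that the comparison is biased, and biased in favour of NOM. The protocol does not support that. It gives no EQ-5D by response group, and hence neither a gap nor its sign. All patients are stage II or III, ECOG 0-2 and judged at baseline to need TME (section 6.1). Allocation rests on endoscopic, digital and MRI tumour findings (section 9.3.2), so a difference in symptoms or fitness between the groups is conjecture. The 15 to 30 expected cross-overs kept in the NOM group would, if surgery lowers quality of life, pull the contrast the other way. The net direction is unknown.

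The bias and precision figures follow from assumed inputs; they show what could happen, not what has. With 137/90 the t-test already detects about .057, close to the lower minimally important difference, so the precision argument weighs less than the stated group sizes suggest. Registration EQ-5D precedes all therapy and cannot be expected to remove all confounding by response. Nor is adjustment free: a patient with a 1-year score but no registration score must be handled. Finally, this is a secondary objective of a phase II trial, and the SAP is not at hand.

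These points limit the strength of the finding but do not remove it. The protocol itself names the test, so this is not a detail left to the SAP, and no section supplies an adjusted primary QoL analysis. Keeping cross-overs in the NOM group preserves the initial assignment by response; it does not make the groups comparable.

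**Conclusion.** The point holds in this form: the primary QoL comparison is an unadjusted contrast of non-randomised groups, open to confounding of unknown size and direction, and it leaves a collected pre-treatment score unused. The significance-based choice of covariates in the 1-to-3-year model is a weak rule in its own right. The stated power is correct for the test named.

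Under the assumed correlation of .4 to .6, the detectable difference would fall from about .057 to .052-.046 at 137/90, or from .069 to .063-.055 at 94/62. An assumed gap of .03 to .05 at slope .5 would shift the t-test by .015 to .025. None of this shows that the trial's estimate will be wrong, and adjustment would reduce confounding without guaranteeing its removal. The change is worth making because the exposure is avoidable and the cost small.

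**What to change.** In section 14.3, and correspondingly in the SAP:

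- Make the primary QoL analysis an ANCOVA of 1-year EQ-5D on group (NOM or TME), with registration EQ-5D and a pre-specified list: age, sex, ECOG, MRI T and N stage, randomised arm, and tumour distance from the anal verge if recorded. Section 9.3.4.1 implies that distance, but the forms listed in section 16.0.2 do not name it.
- Add re-staging EQ-5D in a sensitivity analysis. It is the score closest to the NOM or TME decision, but section 9.6 does not say whether it is completed before the patient learns the result.
- Use the same fixed list in the 1-to-3-year model in place of selection by significance.
- Keep the t-test as a descriptive result.
- Report the finding as a non-randomised comparison in which residual confounding is possible.
- State how a missing registration score is handled. Section 10.0 requires QoL only of English-fluent patients at US and English-speaking Canadian sites, so the analysed population should be described as well.

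The cost is a wording change, some extra analysis and the missing-score rule. No patients, visits or questionnaires are added.

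### The ANCOVA for 1-to-3-year EQ-5D change picks its covariates by a significance screen between non-randomized groups, so prognostic variables with a moderate imbalance can be dropped

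*Protocol*

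**What the plan says.** All of this is in Protocol section 14.3 (secondary objective 2) unless noted.

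- The main QoL comparison is EQ-5D index at one year, NOM against TME, with no adjustment: "Comparison will be done using the two-sample t-test". The durable-NOM comparison at one year is also a t-test.
- One further secondary analysis is adjusted, namely that of the change in EQ-5D index between the one-year and three-year surveys. Its covariates are fixed by this rule: "using an ANCOVA model that adjusts for variables found to be significantly different by NOM vs TME". No candidate list and no selection level are given, and the candidates are not limited to baseline variables.
- The section closes by extending analyses of the same kind to the remaining functional and QoL endpoints, so the rule carries over to them.
- Group sizes: "Thus, at 1 year we expect to have information on 94 TME patients and 62 NOM patients". The expected split of all 325 patients is 129 NOM and 196 TME. Some 15 to 30 NOM patients are expected to cross over, and the durable-NOM analysis counts them as TME.
- Section 9.3.2 assigns patients by response at re-staging: complete or near complete response goes to NOM, incomplete response to TME.

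**The concern.** The protocol itself fixes this rule, so it is more than a detail left for a later SAP.

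Whether a variable confounds the NOM-TME comparison depends on two things: how far it differs between the groups, and how strongly it is related to the outcome. The screen looks only at the first, and does so through a p-value, which also reflects sample size. A prognostic variable with a moderate real imbalance can miss significance and be left out, while a variable unrelated to QoL can be let in. The covariate set is also chosen from the data being analysed. Baseline EQ-5D, an obvious candidate, enters only if it happens to pass.

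This is the only adjusted QoL analysis that section 14.3 describes. Readers will turn to it when they ask whether a NOM-TME difference reflects the patients rather than the treatment, so residual confounding there matters.

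**Working it through.** **1. The plan's own figure.** Inputs from 14.3: 94 TME, 62 NOM, SD .15, difference .07, type I error 5% (two-sided assumed).

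SE in SD units = √(1/62 + 1/94) = 0.1636. Power = Φ(.07/(.15 × 0.1636) − 1.96) = Φ(0.892) = 81%. The stated 80% reproduces.

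**2. Chance that the screen drops a truly imbalanced variable.** The selection level is not stated; 5% two-sided is assumed. For a true imbalance of d SD:

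P(dropped) = Φ(1.96 − d/SE) − Φ(−1.96 − d/SE), with SE = √(1/n₁ + 1/n₂).

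Example at 62/94, d = 0.3: d/SE = 1.834, so P = Φ(0.126) − Φ(−3.79) = 55%.

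The protocol does not say on which patients the screen is run, so three sizes are shown:
- 62/94, the stated one-year respondents;
- 90/137, which is 70% of 129/196 (14.3 expects 70% completion; the stated total of 156 instead matches 70% of the earlier 222 patients, 155.4);
- 129/196, all patients.

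| NOM/TME | SE | d = 0.2 | d = 0.3 | d = 0.4 | d = 0.5 |
|---|---|---|---|---|---|
| 62/94 | 0.1636 | 77% | 55% | 31% | 14% |
| 90/137 | 0.1357 | 69% | 40% | 16% | 4% |
| 129/196 | 0.1134 | 58% | 25% | 6% | 1% |

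If 70% of 30 cross-overs (21 patients) move from NOM to TME at 62/94, the groups become 41/115 and the rates are 80%, 62%, 41% and 21%. No three-year completion rate is given. If the screen uses only patients with both surveys, attrition would raise the rates further.

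**3. Consequence for the comparison.** Simulation with no true group effect, 62/94 both screened and analysed, independent normal confounders each 0.3 SD apart, screen at 5%. The number, strength and direction of the confounders are assumptions.

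| Confounders | Correlation with outcome | False-positive rate, screened | Bias, screened |
|---|---|---|---|
| One | 0.5 | about 6% | 0.05 SD |
| Four, same direction | 0.15 | 6.5% to 7% | 0.06 SD |
| Four, same direction | 0.3 | about 12% | 0.12 SD |
| Four, two in each direction | 0.3 | about 5% | none |

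Adjusting for the same variables without a screen gives about 5% throughout. With one confounder the bias is small because the screen drops it mainly when the observed imbalance happens to be small. Several omitted variables can add up.

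**4. On the EQ-5D scale.** With an SD of .15, 0.05 SD is 0.05 × .15 = .0075 and 0.12 SD is 0.12 × .15 = .018. The protocol gives .15 for the index, not for its change, so this conversion is also an assumption. The protocol's minimally important difference is .05 to .09.

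**The case against.** The strongest reply is that the size of the problem comes from inputs the protocol does not contain. That is right, and it limits the point in four ways.

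- A reader might infer that confounders are omitted about half the time. That holds only for an imbalance near 0.32 SD at 62/94 with a 5% selection level. The 62/94 figures are one-year respondents used to power a different test. Stage and ECOG are recorded for every enrolled patient, and a screen on all 129/196 misses a 0.3-SD imbalance 25% of the time.
- A reader might infer that the false-positive rate is generally inflated. The 12% case needs four confounders all acting in the same direction, each correlated 0.3 with a late change score; together they explain 4 × 0.3² = 36% of its variance. Nothing in the protocol supports or excludes this. Weaker or offsetting confounders bring the rate close to 5%.
- A reader might infer that the protocol takes non-significance as proof of balance. It does not say so; that describes the effect of the rule.
- A reader might infer that fixed adjustment removes bias. In the simulation it does, but only because the simulated confounders are exactly those fitted.

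It is also fair that no trial decision rests on this ANCOVA: the DFS criterion and the pick-the-winner rule do not use it. The unadjusted one-year t-tests are more exposed to confounding.

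What stands is the rule itself. It selects on the wrong criterion in a non-randomized comparison, and a better rule costs almost nothing.

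**Conclusion.** The concern holds as a minor point. The covariate rule for the durable-NOM versus TME comparison of EQ-5D change, and for the analogous analyses of other endpoints, can discard prognostic variables with a moderate real imbalance and does not secure baseline EQ-5D.

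For imbalances of 0.2 to 0.5 SD and an assumed 5% selection level, the chance of omission is 77% to 14% at 62/94, 69% to 4% at 90/137 and 58% to 1% at 129/196. The resulting bias ranges from none to 0.12 SD in the scenarios examined, or at most about .02 on EQ-5D if the SD of the change is .15. That is below the protocol's minimally important difference. The documents do not support a single omission rate or a general claim of inflated type I error.

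**What to change.** In section 14.3, replace the significance screen with a set of baseline covariates named before the outcome data are examined, chosen on clinical grounds and kept whatever their p-values. For example: baseline EQ-5D index (or the baseline value of the endpoint concerned), age, sex, clinical T and N stage, tumor distance from the anal verge, ECOG status and randomized arm. State that the same set applies to the analogous analyses of the other patient-reported endpoints.

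The cost is one sentence and a few degrees of freedom. The protocol already plans most of these data: the QoL survey at registration (9.6), ECOG and MRI at pretreatment evaluation (8.2), tumor margins relative to the anal verge at endoscopy (9.3.4.1), and arm (15.2).

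The change reduces measured baseline confounding only. It does not remove selection by tumor response, or the selection that comes from defining durable NOM by three-year disease-free survival. It also leaves the one-year t-tests unadjusted; using the same covariates there as a supporting analysis would be a natural addition.

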#### **14.4 Correlative studies: objectives**

The correlatives studies will be conducted in patients accrued at MSKCC only. During the past five years, an average of 120 patients with stage II and III rectal cancer have been treated at MSKCC; 43 of them had tumors located within 6 cm from the anal verge, and are potentially eligible for the trial. We estimate that 20 patients (less than 50% of eligible patients) will be accrued to the trial every year, for a total of 80 patients over the 4-year accrual period. Assuming equal distribution between arms, we anticipate that 56 patients will ultimately be treated with TME and 24 with NOM.

Endpoints for each of the aims will be compared between patients treated with TME and patients treated with NOM. Endpoints for each of the aims are as follows:

*14.4.1 To investigate the diagnostic performance of conventional and diffusion-weighted magnetic resonance imaging (DW-MRI) in identifying patients with LARC treated with TNT, who may benefit from NOM.*

Measurements used for correlation include mrTRG in T2-w imaging, assessment of DW signal intensity (SI), mrΔvolume between baseline and post-TNT examinations in both T2-w and DW imaging, and changes in ADC, true diffusion (D), and perfusion fraction (f) between baseline and post-TNT DW-MRI. The outcome will be the proportion of patients treated successfully with NOM, meaning the patient is free of disease at the 3-year endpoint, plus patients with ypT0 after TME.

This will be the first study investigating the diagnostic performance of conventional and DW-MRI in LARC patients treated with TNT and NOM. Therefore, this aim will be considered exploratory.

DW-MRI will be done for all MSKCC patients. Participating sites may perform DW-MRI, but this is not required. If one exam for a patient is performed as DW-MRI, all subsequent exams for the patient should be done using the same technique. If performed, DW-MRI will be captured in the appropriate case report forms.

*14.4.2 To evaluate the feasibility of using circulating tumor DNA and miRNA profiles in plasma to monitor tumor response to TNT in rectal cancer patients treated in both protocol arms.*

The measurement will be the presence of tumor specific mutations—defined as mutations present in the pretreatment biopsy—in plasma DNA of patients in both study groups at different time points (see Section 10.0). A second measurement for this aim will be the plasma miRNA profiles at the same time points as above. We will graphically examine these two measurements in patients treated successfully with NOM plus patients with ypT0 after TME and with patients who had residual tumor after TME.

As this will be the first prospective study investigating the circulating tumor DNA and miRNA profiles in rectal cancer patients treated with TNT and NOM, this aim will be considered exploratory.

Patients who take part in this portion of the study will be from Memorial Sloan Kettering only. Given the smaller sample size, all analyses will be descriptive. We will graph each measurement over time for the two groups defined above. If possible, comparisons at each time point will be done using nonparametric methods, such as the Wilcoxon rank-sum test.

*14.4.3 Use of genomic analysis by next generation sequencing to profile rectal cancer treated with neoadjuvant chemotherapy and radiation.*

The measurements for this study will be the mutation profile, copy number alteration profile, and gene expression profile in pretreatment tumor biopsies of patients treated in both study arms. We will compare the results in patients treated successfully with NOM plus patients with ypT0 after TME, with patients who had residual tumor after TME.

As this will be the first prospective study investigating the genomic profile of rectal cancer patients treated with TNT and NOM, this aim will be considered exploratory.

*14.4.4 Investigation of the molecular mechanisms of tumor resistance to neoadjuvant therapy by genomic analysis of rectal cancer before and after treatment.*

The endpoint for this study will be the proportion of cells expressing the colonic stem cell biomarkers in pretreatment tumor biopsies of patients treated in both groups. We will compare the results in patients treated successfully with NOM plus patients with ypT0 after TME and compare them with patients who had residual tumor after TME. In addition we will investigate the expression of colonic stem cell biomarkers in the surgical specimens of patients with residual tumor after TME.

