| Endoscopic Exam     | 
 
• Flat whitish scar
 
• Telangiectasia
 
• No ulcer
 
• No nodularity
 
                                                                                                         | 
 
• Irregular mucosa
 
• Small mucosal nodules
 
• Superficial ulceration
 
• Mild persisting erythema of the scar
 
 | 
 
• Visible tumor
 
                                                                                        |
| Digital Rectal Exam | 
 
• Normal
 
                                                                                                                                                                                           | 
 
• Smooth induration or minor mucosal abnormalities
 
                                                                                    | 
 
• Palpable tumor nodules
 
                                                                               |
| MRI-T2W             | 
 
• Normal appearing bowel wall without any fibrosis in the tumor bed
 
• Only dark T2 signal, no intermediate T2 signal
 
• No visible lymph nodes or very few, small (<5mm nodes)
 
 | 
 
• Mostly dark T2 signal, some remaining intermediate signal
AND/OR
 
• Partial regression of lymph nodes
 
                   | 
 
• More intermediate than dark T2 signal, no T2 scar
AND/OR
 
• No regression of lymph nodes
 
 |

|               |                                                                                                                                                                                                                                            |                                                                                                    |                                                                                                      |

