### **9.5.1 Volumetry**

Tumor will be identified on 3 types of sequences for volumetry: T2W, DWI and DCE. On each axial slice where tumor is recognized, a free-hand ROI will be traced to enclose tumor and any necrosis, excluding vessels, artifact and luminal contents. The area, automatically calculated by the picture archiving and communications systems (PACS), will be multiplied by number of slices and slice thickness to derive the  $\text{cm}^3$  volume.

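### The correlative endpoints in 14.4.1 to 14.4.4 pool ypT0 after TME with successful NOM and set no nodal condition, so a ypT0 node-positive patient is grouped with the responders

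*Protocol*

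**What the plan says.** Section 14.4.1 (diagnostic performance of MRI) defines one outcome: successful NOM, meaning "free of disease at the 3-year endpoint, plus patients with ypT0 after TME". No nodal condition is attached to the TME part, "plus patients with ypT0 after TME".

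Section 14.4.2 (circulating tumour DNA and miRNA) displays its measurements in "patients treated successfully with NOM plus patients with ypT0 after TME and with patients who had residual tumor after TME". Section 14.4.3 (genomic profile) compares "patients treated successfully with NOM plus patients with ypT0 after TME, with patients who had residual tumor after TME". Section 14.4.4 (stem-cell markers) uses the same two groups. Residual tumour after TME is not defined in any of them.

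Other sections that bear on the point:
- Section 6.1 admits Stage III disease with any T and positive nodes.
- Section 9.3.2 lists "No regression of lymph nodes" on T2-weighted MRI under Incomplete Response.
- Section 9.3.3 treats new or enlarging nodes as signs of re-growth during NOM.
- Section 4.2 already requires AJCC staging of the surgical specimen, so nodal status will be on record.

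**The concern.** The ypT category describes the primary site. A specimen can be ypT0 and still hold tumour in mesorectal nodes. As worded, section 14.4 puts such a patient with the NOM successes.

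This matters for three reasons. First, the composite in 14.4.1 applies two standards: its NOM half requires no disease anywhere at 3 years, while its TME half looks only at the bowel wall. Second, the purpose of 14.4.1 is to find patients who may benefit from NOM, and section 3.5 names undetected residual cancer cells in surgical specimens as the main obstacle to NOM. A patient with nodal cancer in the specimen does not fit the group that the aim is meant to find. Third, in 14.4.2 to 14.4.4 the two groups being compared are not clearly exclusive. The genomic aim is the most exposed: section 3.7 reports that copy number alterations are associated with lymph node metastasis as well as tumour response, and 14.4.3 names the copy number profile as a measurement.

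**Working it through.** **Where a ypT0 node-positive patient falls**

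| Section | Favourable group | Comparison group | Residual tumour includes nodes | Residual tumour means bowel wall only |
|---|---|---|---|---|
| 14.4.1 | NOM success + ypT0 | none named | counted as may benefit from NOM | counted as may benefit from NOM |
| 14.4.2 to 14.4.4 | NOM success + ypT0 | residual tumour after TME | in both groups | responder side only, with nodal cancer |

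Neither reading of the undefined term puts this patient in the residual-tumour group alone. In 14.4.1 the classification does not depend on that term.

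**Expected sample (14.4)**

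20 patients a year × 4 years = 80, and 56 TME + 24 NOM = 80. Both reproduce. No figure stated in the protocol is in dispute.

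**How many patients are affected**

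Number affected = 56 × (ypT0 share of TME specimens) × (node-positive share of ypT0 specimens).

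The protocol gives neither share, so both are assumptions:
- ypT0 share: 7% to 38%, the span of the pCR rates quoted in sections 3.2.2.1 and 3.2.2.2, used as a stand-in. The top is probably too high here, because patients sent straight to TME are those with incomplete response.
- Node-positive share of ypT0 specimens: 2% to 15%, a pure assumption.

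| ypT0 share | Node-positive share | ypT0 patients | ypT0 node-positive | Chance of at least one, 1 − (1 − product of shares)^56 |
|---|---|---|---|---|
| 7% | 2% | 3.9 | 0.08 | 0.08 |
| 14% | 5% | 7.8 | 0.39 | 0.33 |
| 14% | 10% | 7.8 | 0.78 | 0.55 |
| 25% | 10% | 14.0 | 1.40 | 0.76 |
| 38% | 15% | 21.3 | 3.19 | 0.96 |

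With a narrower assumption (ypT0 10% to 20%, node-positive 5% to 15%) the count runs from 56 × 0.10 × 0.05 = 0.28 to 56 × 0.20 × 0.15 = 1.68.

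**As a share of the favourable group**

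If all 24 NOM patients succeed, the wide range gives 0.08 / (24 + 3.9) = 0.3% to 3.19 / (24 + 21.3) = 7.0%. The narrower range gives 0.28 / (24 + 5.6) = 0.9% to 1.68 / (24 + 11.2) = 4.8%. If fewer NOM patients succeed, these shares rise somewhat.

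**The case against.** **Overlap.** Set against ypT0, residual tumour can be read as its natural complement, tumour in the bowel wall, and then nobody is in two groups. For 14.4.3 and 14.4.4, whose comparisons use pretreatment biopsies of the primary, a bowel-wall contrast is defensible. This stands in part. The overlap is conditional on an undefined term, and a reader who infers that the groups certainly overlap goes further than the text. But the bowel-wall reading leaves a patient with residual nodal cancer among the responders, and it does nothing for 14.4.1.

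**MRI scoring.** Because nodes enter the T2-weighted criteria in 9.3.2, a reader might infer that an MRI which correctly reports persistent nodes is scored as an error under 14.4.1. The protocol does not support this. The measurements named in 14.4.1 are tumour regression grade, diffusion signal intensity, volume change, ADC, true diffusion and perfusion fraction; none is nodal. For volumetry, "a free-hand ROI will be traced to enclose tumor and any necrosis, excluding vessels, artifact and luminal contents", with no mention of nodes. The 9.3.2 schema assigns patients to NOM or TME and is not named as the index test. The list of measurements is open-ended, so the inference is possible but not stated.

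**Terminology.** The protocol does not call ypT0 a complete response. It has a separate term, pCR, and does not use it in 14.4.

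**Weight.** Aims 14.4.1 to 14.4.3 are declared exploratory, 14.4.2 is descriptive, all are MSKCC-only, and detail of this kind could go in an analysis plan. That limits the priority. It does not remove the point, because the protocol itself fixes ypT0 as the criterion.

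**Conclusion.** The point holds as a definitional fault of minor priority. All four correlative endpoints use ypT0 without a nodal condition. In 14.4.1 this counts a ypT0 node-positive patient as one who may benefit from NOM, at odds with the disease-free requirement in the other half of the same outcome. In 14.4.2 to 14.4.4 the patient is either in both groups or on the responder side with cancer in the specimen, depending on what residual tumour means.

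The size is roughly 0 to 3 of 56 TME patients, and it rests entirely on assumed rates. Any misassignment runs one way, towards the responder group. No primary or secondary endpoint, stopping rule or arm-selection rule uses ypT0.

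**What to change.** In 14.4.1 to 14.4.4, replace ypT0 after TME with ypT0N0 after TME. In 14.4.2 to 14.4.4, define residual tumour after TME as its complement: any viable tumour in the bowel wall or the nodes. A ypT0 node-positive patient then falls in exactly one group, and both halves of the 14.4.1 outcome treat nodal disease alike.

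Where a measurement concerns the primary tumour only, a bowel-wall (ypT0) grouping can be shown as a sensitivity analysis, labelled as such.

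The cost is wording. Pathological staging is already required by section 4.2, so no new data are needed. The responder group may be a few patients smaller.
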